## Methods: Monitoring

### Data monitoring

#### Composition of the data monitoring committee, its role and reporting structure {21a}

We did not need a data monitoring committee since there are no intervention groups. All patients we recruited from the neurophysiology department of the Vigen Macarena Hospital (Seville, Spain), who underwent an ultrasonography following a specific protocol and therefore patients were not randomized.

#### Interim analyses {21b}

No interim analysis will be performed.

### Harms {22}

Although the diagnostic tests evaluated in this study are harmless for humans, we have to consider the possibility or adverse effects, and how we will collect them when applying the test throughout the study.

On the one hand, at the end of the ultrasound, we will collect the appearance of any adverse effect by answering a Yes / No question, and if so, a brief description of it. If the adverse effect come up hours after the test was carried out, all patients have, in their informed consent copy, an email address of the principal investigator that they can attend.

Regarding the possible side effects derived from the neurophysiological test, being a different department from Rehabilitation, Regarding the possible side effects derived from the neurophysiological test, being a different department from Rehabilitation, it is they who manage the appearance of these adverse effects as part of their daily clinical activity.

### Auditing {23}

Of the two main researchers, one of them will carry out the ultrasounds and data collection, while the other one will carry out the quality control of the study, a well-done data collection, the proper functioning of the ultrasound system, the appointment of patients, etc.

## Discussion

This protocol describes a prospective, cross-sectional study that compares electroneurography and ultrasound in the diagnosis of CTS. The median nerve undergoes physiological changes including swelling and edema as it is compressed within the tunnel, resulting in increased CSA and hypoechogenicity. In advanced CTS, inflammation of the nerve leads to hypervascularisation, which can be detected by Doppler. Ultrasonography allows not only to objectify median nerve alterations but also the underlying pathological mechanisms in CTS. In turn, ultrasound can also be useful to assess underlying structural causes of CTS, such as cysts, ganglions or the presence of other masses invading the tunnel [21]. It is important to note that in early stages, morphology may not be affected, so in the presence of normal ultrasound findings in patients with suggestive symptoms, we should not exclude the diagnosis of CTS [22].

Regarding the sensitivity and specificity of ultrasound, the values obtained in one study were of 78% for sensitivity and 87% for specificity [23], with values of up to 94% sensitivity and 98% specificity having been described in the literature [24].

It should be emphasized that ultrasound is operator dependent [25], therefore good training is very important to ensure reliability and reproducibility.

If we analyze the ultrasound assessment protocols described to date, there has been much disparity between scientific publications; like Roll et al. [26], we consider this to be the main reason why there is no standardized protocol for ultrasound study as a diagnostic test. The authors Chen et al. [10] proposed an ultrasound assessment protocol that included patient position and ultrasound parameters such as CSA at the entrance and exit of the tunnel, CSA in the distal third of the forearm, longitudinal view of the nerve, and dynamic tests (when flexing the first finger and when flexing the rest of the fingers) both to observe changes in the diameter of the nerve without measurement, and lumbrical tests (to determine whether they invade the tunnel when making a full grip).

In our study, we have based ourselves on the general lines described in this protocol, adding other parameters based on the literature review.

Among the ultrasound parameters analyzed, Duncan et al. were the first to demonstrate the superiority of the CSA over the other ultrasound parameters [25], although there are authors [27] who have suggested the superiority of the nerve inflammation ratio over the rest. In turn, Swen et al. established that the optimal atomic reference for measuring CSA is the entrance of the tunnel at the level of the pisiform [28].

As Hobson-Webb et al. [29] have already stated, a single measurement can result in a false positive, so in our protocol we have decided to take the mean of 3 consecutive CSA measurements of the median nerve, but not for the indices or retinaculum ballooning.

Regarding the cut-off point for CSA, a lot of variability is reported in the literature. Considered normal limits of nerve CSA range from 7 to 9.4 mm2 [30], and critical values vary from 9 to 15 mm^2^ [31]. This variability is mainly due to the different measurement techniques used between studies. It does seem clear that the area of the median nerve increases as the syndrome progresses over time [32].

In relation to the diagnostic accuracy of the CSA parameter, the most extensive review carried out in this regard dates from 2012 by Cartwright et al. [33], who concluded that ultrasound "probably adds value to nerve conduction studies in the diagnosis of CTS for detecting associated anatomical alterations” and recommended "using ultrasound as a screening tool to assess structural alterations in patients with suspected CTS".

In our study, we included both patients with CTS (confirmed by neurophysiological testing) and patients considered "healthy" (with negative neurophysiological testing), in order to analyze the ultrasound differences between the two groups. Hobson-Webb et al. [29] observed that the CSA in healthy patients was lower than in patients with CTS, with values of 10 mm2, higher than that reported by authors such as Hammer et al. [34] or Yesildag [35], but similar to that reported by others such as Nakamichi and Tachibana [36].

In relation to the wrist-forearm index, the first to consider this parameter were Hobson-Webb and his team, who observed that in normal subjects the CSA in the wrist has been described as having the same value as that of the forearm and hypothesized that the ratio between the two could be a diagnostic alternative [29], on this basis, the wrist-forearm index should be 1:1. Both Hobson-Webb et al. [29] and Mhoon et al. [37] observed that values of 1.4 or higher have a high sensitivity (97–100%) to diagnose CTS and values below 1.4 a high sensitivity (99%) to rule it out, the low specificity (28%) limiting its use to screening only.

In our study, based on the approach of Hobson-Web et al. [29], we measured CSA at the tunnel entrance and 12 cm from the distal wrist crease. There are authors who have performed this index using different measurement references [38], so we will not, at the time, establish a comparison between their findings and those of our study. We took 1.4 as the cut-off point, as it is the most frequently considered cut-off point.

In relation to the Doppler tool, its usefulness lies in the fact that in healthy subjects intraneural blood flow has never been demonstrated, which seems to reflect a pathological condition. It has been observed that Doppler can detect increased intraneural or epineural vascular flow in patients with CTS, which seems to reinforce the diagnosis [39], and a correlation has been observed between intraneural flow and CTS severity [40].

When applying the doppler, the position of the wrist is very important, which could also influence blood flow.; the authors Vanderschueren et al. recommend keeping the wrist in a neutral position, avoiding mobilization of the fingers or provocation tests [41].

Another parameter studied over time has been the thickening of the flexor retinaculum in the proximal region of the carpal tunnel, the interest being based on the fact that continued inflammation and the consequent extraneural reactive fibrosis cause a greater thickness of this structure, considered in the pathological range above 1 mm [42]. In any case, in our opinion, like Pardal-Fernández [43], we consider it to be a parameter of low sensitivity, due to the small size of its dimensions and the consequent variability in measurements.

The flattening ratio is a ratio between the transverse and anteroposterior diameters in the intracarpal region, described within the tunnel. It is a well-regarded parameter [44] and ratios above 3.5–4 are considered pathological. At the mid-distal level, in the ulnar nerve, some authors have shown that the trapped nerve presents a morphological deformation of its floor, in such a way that it outlines the contour or ridge of the tendons it contacts, showing a deformity similar to a “triangular” [45]. In turn, the authors Lee et al. analyzed different ultrasound variables including the flattening index, but at different levels of the tunnel: at the pisiform, hamate and lunate. Statistically significant differences were only obtained between both groups in the measurement made at the level of the hamate (cut-off point 3. 2+/-0.4 P<0.05) [46]. These same results were found by Tai et al. in a meta-analysis carried out in 2012 [47]. In any case, some authors did not find cost-effectiveness in this parameter [48]. We have included it in our parameters and hope to clarify its usefulness.

The flexor retinaculum may bulge as a result of increased intracarpal pressure. The buckling of the flexor retinaculum, in most CTSs, is usually not important considering the low elasticity of this structure, especially if it is also fibrosed. In any case and taking into account that the image at this point is not usually good, these findings are not very conclusive due to their low reproducibility. We have included this parameter in our measurements, finding it useful based on the literature analyzed and hoping to clarify the best cut-off point.

The mobility patterns of the nerve in patients with CTS have also been analyzed. Chen et al. [10] also included in their protocol a "stress test" when flexing the first finger and when flexing the rest of the fingers (changes in the diameter of the nerve without measuring) as well as the lumbrical test (to determine whether they invade the tunnel when performing a full grip). We found the performance and assessment of these tests to be highly dependent on the experience of the examiner, which is why we have dispensed with dynamic tests in the development of our protocol.

The last two "items" that we analyzed in our study are, on the one hand, the search for anatomical alterations that may compress the median nerve as it passes through the tunnel (ganglions, tendonitis, etc.), since ultrasound allows easy detection of anatomical alterations of the nerve [36]. In our study, as described above, we performed a scan of the image in both the transverse and longitudinal planes, covering all structures from lateral to medial.

On the other hand, we assessed the presence of nerve grimacing in the longitudinal plane, to identify whether there is a specific point of compression. In general, the nerve increases in size immediately after the compression zone.

We have included the BCTQ scale, a validated, self-administered instrument that assesses the impact of CTS on both symptoms and patient function [49], and a statistically significant relationship has been demonstrated between CSA, NPT score, clinical symptoms and hand function [14,15]. Contrary to this, Mondelli et al. in 2008 [16] found no relationship when comparing the combination of ultrasound and NPT score versus BCTQ.

When comparing neurophysiological studies versus ultrasound, although the former offer 85% sensitivity and 95% specificity in the diagnosis of CTS, they are invasive and unpleasant for the patient [12]; recent literature has shown that patients themselves have a preference for ultrasound over nerve conduction studies [49].

Although the specificity of neurophysiological tests is high, there is significant variability in their sensitivity (56–85%) which can translate into false negative results between 10–20% of patients [33] and false positives between 16–34% [50]. Other authors report an NPT sensitivity of 88% and specificity of 93% [44].

Although ultrasound may not replace neurophysiological testing as the gold standard for confirmation, authors Fowler and Gaughan suggest that it could be proposed as a first-line tool [50]; they add that the best candidates for ultrasound are those with high prior probability based on examination and reported symptomatology. Several authors [33,51] propose ultrasound as an initial screening test, leaving nerve conduction for definitive diagnosis.

The use of ultrasound as a diagnostic tool in CTS has many advantages for both the physician and the patient. It is a non-invasive, convenient, and fast tool, and ultrasound equipment is becoming increasingly cheaper, making it more accessible to the healthcare system [21].

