## Statistical methods

### Statistical methods for primary and secondary outcomes {20a}

After an initial exploration of the data, quantitative variables are expressed as means and standard deviations or medians and quartiles in case of asymmetric distributions, and qualitative variables as percentages.

The calculation of the measures of test accuracy of the ultrasound test as a diagnostic test for CTS: sensitivity, specificity, predictive values and likelihood ratios, are carried out considering the neurophysiological study as the reference test (gold standard).

Likewise, the reliability of the ultrasound is analyzed by calculating the degree of agreement between the diagnoses of the two tests using Cohen’s Kappa coefficient. The concordance of both tests with the established clinical severity is also studied.

The analysis of the quantitative variables did not present normality (Gaussian assumptions), therefore, for statistical inference, the Mann Whitney test (violations of Gaussianity) was used for independent quantitative variables. Shortly afterwards, a multivariate logistic regression model will be created to try to determine the best subset of them that predict CTS [20].

Finally, ROC curves will be performed to evaluate cut-off points for certain quantitative ultrasound parameters that discriminate well against CTS. In the ROC curves, the optimal cut-off point for greater sensitivity and specificity was determined by using the Youden index. In those ultrasound parameters where the ROC curve did not allow adequate discrimination, the median value of the data distribution was used.

In summary, the univariate analysis aims to identify which ultrasound parameters are related to the result of the CTS, thus providing elements of analysis to determine the cut-off points to be evaluated by means of ROC or medians, as well as the main variables to be considered in the multivariate model.

Data analysis is performed with SPSS 25.0 statistical software.

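### The protocol fixes the wrist-forearm index cut-off at 1.4 in the Discussion, but its statistical methods derive cut-offs only from the study data and state no exception for the index

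*Protocol article*

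**What the plan says.** **Protocol article, Discussion (wrist-forearm index).** After describing how this study measures the index, the authors write: "We took 1.4 as the cut-off point, as it is the most frequently considered cut-off point". They cite two earlier studies in which "values of 1.4 or higher have a high sensitivity (97–100%) to diagnose CTS", with "the low specificity (28%) limiting its use to screening only".

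**Protocol article, section {20a}.** Cut-offs come from the study data. "ROC curves will be performed to evaluate cut-off points for certain quantitative ultrasound parameters that discriminate well against CTS", and "the optimal cut-off point for greater sensitivity and specificity was determined by using the Youden index". For the remaining parameters: "In those ultrasound parameters where the ROC curve did not allow adequate discrimination, the median value of the data distribution was used". The closing summary of that section names the same two routes: "determine the cut-off points to be evaluated by means of ROC or medians". No literature-based threshold appears, and the index is not named.

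**Protocol article, sections {7} and {12}.** The index is listed among the ultrasound variables as a ratio of two cross-sectional areas, so it is quantitative. Determining reference values for ultrasound parameters is a secondary objective.

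**The concern.** One quantitative parameter appears to fall under two rules. The Discussion gives it a threshold taken from the literature. Section {20a} sends quantitative parameters to Youden or to the median according to how well they discriminate in the sample, and 1.4 comes from neither route.

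The cut-off determines which patients count as index-positive. It therefore determines the index's sensitivity, specificity, predictive values and likelihood ratios, and the reference value that the study hopes to propose. While both rules stand in the text, either result could be presented as following the protocol after both have been seen. Of the two, only the 1.4 rule is set outside the study data, so only its accuracy estimate is free of cut-off selection.

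**Working it through.** **1. The two texts side by side**

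| | Discussion | Section {20a} |
|---|---|---|
| Source of cut-off | Published value, 1.4 | Study data: Youden, or median if the ROC curve discriminates poorly |
| Applies to | Wrist-forearm index, by name | Certain quantitative ultrasound parameters, not listed |
| Refers to the other rule | No | No |

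The word for "ROC curves will be performed to evaluate cut-off points for certain quantitative ultrasound parameters that discriminate well against CTS" leaves room for an exemption. However, the split that {20a} actually describes is by observed discrimination, not by whether a published threshold exists. A reader has to supply the exemption.

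**2. The plan's own planning figure.** With n = z² p(1 − p) / 0.05² and z = 1.96:
- p = 0.78 gives 263.7, rounded up to 264 NPT-positive patients.
- p = 0.87 gives 173.8, rounded up to 174 NPT-negative patients.
- The total is 438, as in Table 3. The sample size reproduces and is not in question here.

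**3. How far the two rules could diverge**

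Inputs from the Discussion: sensitivity 97–100% and specificity 28% at 1.4. The documents give no distribution for the index. Assumption: after a suitable monotone transformation it is normal in both groups. Sensitivity is taken as 97–99%, because the model has no finite solution at 100%.

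*Equal SDs.* The separation is d = z(sensitivity) + z(specificity), and at the Youden point sensitivity = specificity = Φ(d/2).

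| Sensitivity at 1.4 | d | Sensitivity = specificity at Youden | Specificity minus 28% |
|---|---|---|---|
| 97% | 1.881 − 0.583 = 1.298 | 74.2% | +46 points |
| 98% | 2.054 − 0.583 = 1.471 | 76.9% | +49 points |
| 99% | 2.326 − 0.583 = 1.744 | 80.8% | +53 points |

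Sensitivity falls over the same step: 97 − 74.2 = 22.8 points in the first row and 99 − 80.8 = 18.2 points in the last.

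*Unequal SDs.* Set the NPT-negative SD to 1 and the NPT-positive SD to r. Hold the curve at the cited operating point and search for the maximum of sensitivity + specificity − 1.

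| r | Specificity gain, 97% at 1.4 | Specificity gain, 99% at 1.4 |
|---|---|---|
| 0.5 | +12 | +22 |
| 0.67 | +25 | +35 |
| 1 | +46 | +53 |
| 1.5 | +60 | +63 |
| 2 | +65 | +67 |

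The matching loss of sensitivity is about 8 to 23 points.

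*Median rule.* Section {20a} uses the median only when discrimination is inadequate. In the limiting case of no discrimination, half of each group lies above the median, so specificity is 50%, and 50 − 28 = 22 points.

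**4. How much of this is bias.** Simulating 264 and 174 patients under the equal-SD model (3,000 samples at each of the three values of d), and choosing and evaluating the Youden cut-off in the same patients, overstates sensitivity by about 1.3–1.5 points and specificity by about 1.5–1.9 points. The rest of the gap is movement along one ROC curve.

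**The case against.** The strongest reply is that the texts can be read together. Section {20a} restricts ROC analysis to certain parameters and does not name the index. The Discussion is the only text specific to the index, and it commits to one value. For the retinaculum bulge, by contrast, the authors say they hope to find the best cut-off, and they say nothing similar for the index. A specific rule may govern the index while a general rule governs the rest. This stands to the extent that a reader who infers two incompatible rules goes further than the text does. It does not remove the gap: the summary in {20a} lists only ROC or medians, and neither place states an exemption.

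A reader might also infer that specificity would differ by about 50 points. The documents do not support a single figure. It needs equal spread in the two groups, which nothing in the protocol establishes. It also rests on a specificity of 28% from other studies, which may not carry over to symptomatic NPT-negative patients here.

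Nor does the gap measure bias. It is mainly an exchange of sensitivity for specificity, and the optimism from choosing the cut-off is only 1–2 points. The 5-point precision in section {14} was set for ultrasound as a diagnostic test, not for this index, so it is not the yardstick. That the choice would follow the more favourable result is a possibility the text leaves open, not something it shows.

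Finally, a condensed article may leave the list of ROC parameters to a fuller document. That would excuse silence. Here the article states two rules and does not say how they relate.

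**Conclusion.** The point holds as an unreconciled pair of statements about one secondary parameter. The protocol says the index is cut at 1.4, and separately describes only Youden or median cut-offs for quantitative ultrasound parameters. Which of these produces the index's reported accuracy and reference value is not settled.

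The possible effect on specificity is substantial but uncertain: about 46–53 points under an equal-variance binormal model, about 12–67 points for SD ratios of 0.5 to 2, and 22 points for the median with no discrimination. All of these are conditional on the cited operating point at 1.4. The correction is worth making because reference values are a stated secondary objective and the change is very small.

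**What to change.** Add to section {20a}:

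- The accuracy of the wrist-forearm index is reported at the pre-specified cut-off of 1.4, as the Discussion already says.
- Any Youden-derived cut-off for the index is exploratory. It is reported beside the 1.4 result with an optimism correction (for example bootstrap) and does not replace it.
- The sample-median rule is not used for the index.

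The Discussion should then refer to that statement. The secondary objective on reference values is still served, because a data-derived value may be shown and labelled as exploratory.

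The cost is a sentence in the statistical methods and, if a Youden cut-off is reported, a routine resampling step. The one downside is that the index's headline accuracy may look less favourable than at a cut-off chosen from the data.

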## Ethics and dissemination

### Research ethics approval {24}

This study has been approved by the Andalusian Biomedical Research Ethics Committee (Comité de Ética de la Investigación Biomédica de Andalucía). Written informed consent will be obtained from all participants before entering in the study.

### Protocol amendments {25}

We will communicate it by email with the relevant parts, as the secondary investigators or the statistician.

